#### Data collection

Self-report questionnaires will be completed electronically on a personal computer, mobile phone or tablet device, or in the facility using a tablet device (Samsung Tab, iPad, or Microsoft Surface) provided by MLSE LaunchPad. Participants under the age of 8 or requiring assistance will be assisted by an adult. Participants aged 8 and over may complete questionnaires independently, but staff assistance will be offered.

Pedometer data will be collected using PiezoRx pedometers for 1 week at each research assessment time-point according to manufacturer’s instructions. Participants will be instructed on how to attach the pedometer to the waist line of clothing, to not open or tamper with the case, and to wear the device at all times unless sleeping or in water. When the pedometer is returned after 7 days, the data will be uploaded to an electronic database using minutes of activity in the Moderate to Vigorous range based on the criterion of 100 steps per minute outlined by PiezoRx.

Focus groups will be conducted annually with participants to gather personal perspectives regarding experience of programs and facility processes and impact of program involvement. Discussions will focus on: the impact of participation on health behaviours, life skills, academic engagement, job readiness and employment, and other impacts not explicitly expected or defined; the trajectory of involvement and access to programs, and wrap-around services offered in the facility.

#### Incentivization

As attendance in programs is expected to mediate anticipated outcomes of participation in programs, strategies will be used to increase youth engagement and facilitate ongoing, regular participation in registered programs. The use of a gamified digital infrastructure to incentivise target behaviours such as attendance and provide external motivation to complete research requirements will be used. A customized mobile website will centralize incentivization of program participation and research-related activities and points will be allocated for various behaviours such as attendance, early registration, completion of research questionnaires, and demonstration of positive health behaviours and key life skills. The points earned can be exchanged for prizes of the participant’s choosing from a selection of sporting goods, apparel and school supplies.

This method will allow the research team to communicate with participants remotely, collect relevant participation data centrally (i.e. program hours and attendance), and provide participants with a consistent means of accessing information and reminders for participation in both programs and research activities. We expect this strategy will engage participants through competition and goal setting and will also allow the research team to reinforce positive health behaviours and life skills included in program curricula remotely to support development and retainment of PYD assets. Further, we expect the electronic collection of data will improve protocol adherence, data accuracy, user acceptability, and adherence to timelines. Given the potential barrier regarding internet and device access, tablet kiosks will be available in the facility’s atrium to ensure all participants have access to the digital infrastructure and incentive strategy.

#### Data management

Standardized electronic capture forms will be used for all data collection to ensure clarity and ease of entry. All data will be entered electronically and exported into an SPSS (IBM Corp., New York, USA) database on a secure server at MLSE LaunchPad. Participant data will be delinked and accessed only by research staff. All data will be hosted on a secure server that is routinely serviced and backed up by MLSE IT staff. Informed consent forms will be scanned and stored on the server and hard copy documents will be destroyed upon conversion to electronic formatting. The data will be retained indefinitely. Peer audit will be conducted by research staff including research analyst, coordinator, manager, and director who will audit procedures and existing data on a cyclical basis.

#### Data analysis

Preliminary analyses will be conducted after 6, 12, and 24 months of recruitment. All statistical analyses will be completed using either SPSS versions 24/25 (IBM) or *R*. Missingness in data will be evaluated for amount of missing data and patterns in missingness. Based on the results of this evaluation, a single mean value imputation method will be applied as needed.

*Ages 6–12:* Repeated measures ANOVAs will be used to examine the main effect of time on physical literacy scores, self-reported physical activity and rates of continued participation in physical activity, controlling for demographic variables such as age and gender. Moderation analyses will be used to explore the effect of program dosage in terms of the number of programs attended over the course of participation in this study on the relationship between time and change in physical literacy. A similar moderation effect will be explored in the relationship between time and the change in self-reported physical activity levels. Pearson’s product-moment correlation coefficients will also be used to explore the relationship between physical literacy and physical activity levels. A standard multiple regression controlling for age, gender, household income and housing status will be used to identify predictive variables for each of the three primary outcomes. Potential predictors for the change in physical literacy include program dosage, type of program involvement (Sport Plus or Plus Sport), physical literacy score at baseline and physical activity level. Potential predictors for the change in physical activity level and rate of continued participation in sport or physical activity include program dosage, type of program involvement, physical activity level at baseline and physical literacy score.

*Ages 13–18:* Repeated measures ANOVAs will be used to examine the main effect of time on positive health behaviours and each of the six life skills, controlling for demographic variables such as age, gender, household income and race. Moderation analyses will be used to explore the impact of program dosage on the relationship between time and each of the six life skills. Pearson’s product-moment correlation coefficients will also be used to explore the relationship between each of the life skills, positive health behaviors and academic outcomes. Logistic regression will be used to identify predictors of high school graduation for the subset of this age group that would be expected to graduate during the study with possible predictors including scores for each life skill at 2-year follow-up, program dosage and program type, while controlling for gender, household income, housing status and baseline life skills score. The same variables will also be used in a standard multiple regression to identify predictors of continued participation in sport and physical activity in this age group.

*Ages 19–29:* Repeated measures ANOVAs will be used to examine the main effect of time on rate of employment, apprenticeship, or continued training, personal income, and rate of continued participation in physical activity, controlling for demographic variables such as age, education level, household income at baseline and housing status at baseline. Logistic regression will be used to identify predictors of employment status at 2-year follow-up, which may include program type and program dosage (number of programming hours), while controlling for similar demographic variables as identified above for the Repeated Measures ANOVA.

*Qualitative:* Focus groups will be recorded digitally for review and transcription. The transcripts will be coded manually and analyzed using a hermeneutic approach, a cyclical process in which the researcher moves between working with the entire text and smaller parts of the text. This approach educes understanding of the transcribed material by bringing forth existing suppositions and recognizes that the interpreter’s own thoughts play a role in re-awakening the texts’ meaning. Using this approach, the perspectives of MLSE LaunchPad members and staff will be understood and contextualized with reference to PYD and SFD theory through repeated reading of the text and interpretation of the phenomena described. Regular research team meetings will be held to confer on analysis and discuss emergent qualitative findings. Analyzed quantitative and qualitative data will be integrated in reporting and presentation of findings.

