## Methods/design

### Study design

The MLSE LaunchPad trial employs a single-arm, non-randomized within subject quasi-experimental design following a cohort of 350 participants aged 6–29 years old over up to 2-years of self-selected participation in programming at MLSE LaunchPad, a Sport for Development facility in downtown Toronto, ON, Canada. Data collection methods utilize repeated measures of age-specific outcomes according to hypotheses outlined in Table 1 and further described in Table 3 using self-reports and pedometer data at baseline, 6 months, 12 months, and 24 months from baseline. Qualitative assessments will take place annually throughout the data collection period using focus groups with a subset of participants. This protocol was developed in the fall of 2016 and initiated in February 2017. These data will collectively be used to evaluate the effects of intentional sport programming in a community hub on PYD and SFD outcomes in urban youth facing barriers. Moderating variables including age, gender, race, household income, postal code, program type, volume of participation and duration of participation will be explored to understand possible explanatory individual and programmatic elements of significance.

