#### Recruitment

Recruitment of participants began in February 2017 and will continue through September 2019. Participants will be followed for up to two years with data collection to conclude by March 31, 2020. During program registration and within the first week of each program cycle, new participants (and parents/guardians if applicable) will be given information about the research study and the requirements of research participation. If the participant indicates interest, they (and the parent/guardian where applicable) will be taken through the consent process.

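### Single mean imputation, with the mean unspecified, is the only missing-data method named before the repeated measures ANOVAs; filling missed visits with the visit mean would inflate false positives as missingness grows

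*Protocol article*

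**What the plan says.** The Data analysis section of the protocol article gives missing data two sentences. The first is a check: "Missingness in data will be evaluated for amount of missing data and patterns in missingness". The second gives the remedy that follows from it: "a single mean value imputation method will be applied as needed". No other method is named. The text does not say whether the mean is taken over the visit, the person, the items of a scale or the whole data set, or how much missing data would trigger its use.

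The main analyses are repeated measures ANOVAs. For the youngest group, "Repeated measures ANOVAs will be used to examine the main effect of time on physical literacy scores"; for the middle group, "Repeated measures ANOVAs will be used to examine the main effect of time on positive health behaviours and each of the six life skills". The oldest group has the same type of analysis for employment or training placement, income and continued sport participation.

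Outcomes are measured "using self-reports and pedometer data at baseline, 6 months, 12 months, and 24 months from baseline", in a "single-arm, non-randomized within subject quasi-experimental design". On timing, the Recruitment section says: "Recruitment of participants began in February 2017 and will continue through September 2019". It adds: "Participants will be followed for up to two years with data collection to conclude by March 31, 2020".

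**The concern.** A standard repeated measures ANOVA needs a value at every visit. A participant who misses one is either deleted or filled in. A visit-mean fill has two effects. The filled values have no spread of their own, yet each counts as a full observation, so the error variance falls and the F statistic rises. And people who left receive the average outcome of those who stayed, while their own baseline remains in the comparison.

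The study has no control group that would expose a spurious time effect, so it would read as an effect of the program. Two further analyses would suffer. The regression for change in physical literacy lists the baseline score as a possible predictor; for a mean-filled participant, change is a constant minus baseline, which builds in a negative slope. For yes/no outcomes such as placement, mean filling creates fractional values that no participant can have.

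**Working it through.** **1. The plan's own figure.** The article gives no false-positive rate. The nearest figure is 94.9% power at n = 150 for physical literacy (Sample size section). From its inputs, d = (1277 − 1201)/258.8 = 0.294. A one-sample two-sided normal test at 0.05 (assumed; no alpha is stated) gives Φ(0.294 × √150 − 1.96) = Φ(1.64) = 94.9%. The figure reproduces only with all 150 analysed, so planning made no allowance for missing data. (That 0.294 is not the large effect named beside it is a separate matter.)

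**2. Missingness implied by the calendar.** Assume uniform accrual from 1 February 2017 to 30 September 2019, 971 days.

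- 24-month visit by 31 March 2020: baseline needed by 31 March 2018, 423/971 = 44% reachable, 56% not.
- 12-month visit: baseline needed by 31 March 2019, 788/971 = 81% reachable, 19% not.
- 6-month visit: all reachable.

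**3. Closed form for baseline against 24 months.** Let f be the fraction observed at 24 months, ρ the correlation and σ² the variance, with values missing completely at random (MCAR) and filled with the visit mean.

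- True variance of the mean change: (σ²/n)(1/f + 1 − 2ρ).
- Variance the paired test estimates: (σ²/n)(f + 1 − 2fρ).
- Ratio: 1/f, whatever ρ is.

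The nominal 5% test therefore rejects with probability 2Φ(−1.96√f):

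| Missing at 24 months | 1.96√f | False-positive rate |
|---|---|---|
| 5% | 1.910 | 5.6% |
| 20% | 1.753 | 8.0% |
| 30% | 1.640 | 10.1% |
| 56% | 1.300 | 19.4% |

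**4. Simulation of the four-visit ANOVA.** No true change, monotone dropout, MCAR, alpha 0.05. The ranges cover n = 100 and 150 and correlations of 0.3 to 0.7, constant or decaying; n = 150 with correlation 0.5 lies inside them.

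| Missing by 24 months | Visit-mean filling |
|---|---|
| 5% | about 6% |
| 20% | 9–12% |
| 30% | 11–15% |
| 40% | 18–20% |
| Calendar only (0/19/56% at 6/12/24 months) | 19–24% |

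Greenhouse–Geisser correction leaves the calendar case at 18–23%. Filling with the person's own mean or the overall mean stays near 5% (about 2–7%).

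**5. Selective dropout.** Suppose low-baseline youth leave first, with a correlation of 0.3 (assumed) between baseline and the tendency to stay, and ρ = 0.5. With visit-mean filling, the expected spurious 24-month gain in SD units is 0.5 × 0.3 × φ(z)/f, where φ is the normal density at the dropout cut-off z.

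- 20% missing: 0.15 × 0.280/0.80 = 0.05.
- 56% missing: 0.15 × 0.394/0.44 = 0.13.

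Simulated false-positive rates (n = 150) are 12%, 23% and 31% at 20%, 30% and 40% missing, and 41% at calendar-level missingness. The last case is harsh, because the calendar does not itself select on baseline.

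**6. The alternative.** A likelihood-based repeated measures model with unstructured covariance and no imputation (n = 150, ρ = 0.5) gave 4.4–6.1% in every scenario up to 56% missing, MCAR or baseline-dependent, with a shift of about zero. At 65% missing it gave 6.8–7.5% with the simple degrees of freedom used.

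**The case against.** The text is conditional: missingness is examined first and imputation follows only as needed. The mean is not identified. Most outcomes are multi-item scales (physical literacy alone has 22 items), so filling skipped items is a plausible meaning, and under MCAR two of the possible means cause no inflation. The largest figures rest on uniform accrual, which is not stated, and on filling visits that never fell due, although follow-up is described as up to two years. No retention pattern is given, and questionnaires can be completed remotely and earn points of their own, so leaving the program need not mean leaving the study. The Background says the ANOVAs are there to explore the effect. A linear mixed model would also not suit the categorical outcomes.

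Most of this stands, and it limits size and certainty. A reader might infer that every missed visit will be filled with the visit mean, or that the false-positive rate rises several-fold as a fixed consequence of the plan. The documents support neither.

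Three things remain. Examining missingness first cannot lead to a better method, because only one is named; this is a stated choice, not a detail left to an analysis plan. The silence on which mean leaves the result open to a later decision. And person-mean filling is no safe default: filling late visits from earlier scores pulls a real change towards zero.

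**Conclusion.** The concern holds in conditional form. The only named missing-data method is a poor one for these analyses, and it is ambiguous. If the visit mean fills whole missed visits, the false-positive rate is barely raised at 5% missing, roughly doubled at 20%, two to three times nominal at 30%, and about four times nominal at the calendar-implied missingness. That last figure needs uniform accrual and imputation of visits not reached by 31 March 2020. Alpha, correlations and dropout rates are assumptions throughout.

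A reader might also infer a bias in favour of the program. A spurious gain of 0.05–0.13 SD, against 0.29 SD in the sample-size inputs, appears if lower-baseline youth leave more; it reverses if higher-baseline youth do. The article does not say who leaves, so the direction is open.

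**What to change.** - Remove single mean imputation of outcome visits. If mean filling is meant only for skipped items within a scale, say so and state the rule.
- Continuous outcomes: a likelihood-based linear mixed model on all available visits, with visit as a factor and unstructured covariance.
- Categorical outcomes (employment or training placement, continued participation): a generalised linear mixed model or a similar logistic repeated-measures model.
- Where covariates or the regressions need imputation: multiple imputation with baseline score, attendance and demographics in the imputation model.

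The cost is a change of wording and a little more analysis work in SPSS or R, which the plan already names. No new data are needed. The change does not recover 24-month information that the calendar prevents from being collected; it only stops filled values from counting as observations.

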A large, long-term longitudinal study investigating PYD outcomes in a SFD facility for urban youth facing barriers that is based on a clear theory of change illustrating program components is therefore needed. This research is important for both theoretical and practical reasons, and addresses several future research directives published in the field including calls for mixed-methods, longitudinal, and evaluative studies that validate the development of life skills through sport and evaluate the impact of program type of PYD outcomes [26, 30–32]. The current study proposes that participation in theory-based SFD programming at a dedicated facility will lead to increased PYD outcomes in urban youth facing barriers to positive development with age-specific objectives outlined in Table 1 and further articulated in Fig. 1, the Maple Leaf Sports and Entertainment (MLSE) LaunchPad Theory of Change. Repeated measures ANOVAs will be used to explore the effect of long-term participation in MLSE LaunchPad programming on age-specific outcomes. Moderation analyses will be used to identify the impact of program dosage on the relationship between time and primary outcomes. Finally, regression analyses will be used to identify the predictors of primary outcomes to better inform programming.

**Table 1 Tab1:** Study Hypotheses

Primary Hypotheses	
We hypothesize that participation in MLSE LaunchPad programming and wrap around services will result in:	
a) For youth aged 6–12:	• Increased physical literacy • Increased physical activity [28] • Increased rates of continued participation in sport or physical activity [33]
b) For youth aged 12–18:	• Increased positive health behaviors relating to physical activity, sleep, nutrition, smoking, substance use and sexual activity [29, 34] • Increased life skills including critical thinking, resilience, self-esteem, self-regulation, social competence and grit [26] • Increase academic outcomes including school attendance, academic performance and high school graduation rates [26, 34] • Increased rates of continued participation in sport or physical activity [34]
c) For youth aged 19–29:	• Increased rates of placement in employment, apprenticeship, or continued training [26, 29] • Increased personal income • Increased rates of continued participation in sport or physical activity [34, 35]
Secondary Hypotheses	

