#### Sample size

Based on the number of variables planned for analyses in each cohort (see Table 1) [43], we will recruit *n* = 150 youth ages 6–12, *n* = 100 youth ages 13–18 years of age, and n = 150 youth ages 18–29. Statistical power calculations were conducted to justify the appropriateness of the proposed study sample sizes for each age group. For youth aged 6 to 12, statistical power for the primary outcome variable, physical literacy, was analyzed using pre-post MLSE LaunchPad member data on the PLAYself Physical Literacy Assessment tool. To achieve a large effect size (Cohen’s d > = .8; MLSE LaunchPad participant mean = 1201, SD = 258.8; study group mean = 1277), the power calculation performed suggests that the proposed sample size of 150 will yield 94.9% post-hoc power. Power calculations were conducted using data previously collected at MLSE LaunchPad for primary outcome variables of interest in the 13 to 18-year-old cohort (i.e., self-esteem, grit, resilience, physical activity status, and physical activity levels). To achieve large effect sizes for these variables, the proposed sample size of 100 will yield 99.5–100% post-hoc power. Lastly, for youth aged 19 to 29, to achieve a large effect size in the primary outcome variable, employment status, the proposed sample size of 150 will yield 100% post-hoc power (power calculated using data collected at MLSE LaunchPad).

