6–12	Learn to Play (Sport Plus) • Registered, structured 8-week program, 1x/week for 1 h • Coach led according to programming curriculum designed to build sport specific skills, general movement skills, and sport-specific knowledge • Minimal competition • Sport options: basketball, soccer, futsal, ball hockey, football, multisport, rugby, rock climbing, golf, lacrosse, dance, tennis, run club, adapted sport Open Gym (Sport Plus) • Unregistered, semi-structured sport program offered multiple times per week in 1-h blocks • Participant-directed learning that is supported by a coach to develop intrinsic motivation and autonomy, general movement skills, and participant-selected movement and/or sport skills Sport + Nutrition (Sport Plus) • Registered, structured 9-week program, 1x/week for 2 h • On-court physical activities, sports, and games of low organization, plus kitchen activities and nutritional education • Co-led by kitchen instructor and on-court coach • Designed to develop general movement skills, general kitchen skills, and understanding of health concepts (nutrition, physical activity etc.) PA Day Programming (Sport Plus) • Registered 1-day full-day program that includes sport and physical activity programming as well as off-court activities • Program runs on school holidays throughout the school year Day Camp (Sport Plus) • Registered 2-week full-day program that includes sport and physical activity programming as well as off court activities Plus Sport Program Partners • Quantum Sports Learning Association – Registered after-school academic support and athletic coaching program, 1 day/week for 2 h/session • Square Circle – registered after-school social circus program, 2 days/week for 2 h/session • New Leaf Yoga – unregistered after-school yoga program, 1 day/week for 1 h Homework Club Homework support is available from 4 to 6 pm 3 days/week	Increased Physical Literacy Increased Physical Activity Increased rates of participation in sport and physical activity	PLAYself 1-week pedometry Self-report of regular sport/physical activity participation All outcomes are also assessed through scheduled qualitative data collection

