#### Outcomes

Participants will complete a baseline assessment within 2 weeks of recruitment. Follow-up research assessments will take place at 6 months, 12 months, and 24 months from the baseline assessment with data collection concluding March 31, 2020. Outcomes have been identified based on the program theory illustrated in the MLSE LaunchPad Theory of Change (See Fig. 1). Outcomes and indicators for the primary objectives are detailed in Table 3.

**Table 3 Tab3:** Outcomes for Primary Objectives

Participants aged 6–12	
a) Increased physical literacy	Indicator:
	PLAYself Physical Literacy Assessment for Youth [36] 22-item graded self-report scale used to evaluate level of physical literacy
b) Physical activity minutes/day	Indicator:
	One-week pedometry producing at least 3 days of valid data with a minimum wear time of 10 h/day
c) Continued engagement in sport	Indicator:
	Self-report of regular sport/physical activity participation
Participants aged 12–18	
a) Life skills:	Indicator:
i. Critical Thinking ii. Resilience iii. Self-esteem iv. Self-regulation v. Social Competence vi. Grit	Critical Thinking in Everyday Life Scale [37] 20-item self-report Likert scale used to measure use of critical thinking skills including reasoning, enquiry, analysis/information processing, flexibility, and evaluation Child & Youth Resilience Measure [38] 12-item self-report scale used to measure ability to sustain well-being Rosenberg Self Esteem Scale [39] 10-item self-report Likert scale used to assess global self-esteem Motivation and Self-Regulation Subscale; derived from the School Attitudes Assessment Survey [40] 4-item self-report Likert scale used to measure ability to initiate and continue behaviours required to achieve academic goals Social Competence Scale for Teenagers [41] 9-item self-report scale used to measure positive social skills necessary to get along well with others and function constructively in groups Grit Scale [42] 8-item self-report scale used to measure stamina in dimensions of effort and interest
b) Academic Performance:	Indicator:
i. School Attendance ii. Academic Performance iii Academic Attainment	Self-report of number of missed school days over past two weeks measured as a percentage GPA as per last report card; failed courses marked as “R” on TDSB report cards will be input as 45% Self-report of highest grade/level completed
c) Physical Outcomes	Indicator:

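### The itemised analyses do not match the primary outcomes: at ages 6–12 they use a self-reported activity measure with no listed instrument instead of pedometry, and at 13–18 attendance, academic performance and sport participation have no named test of change

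*Protocol article*

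**What the plan says.** **Ages 6–12.** Table 3 (Outcomes section) makes physical activity in minutes per day the second of three primary outcomes. Its indicator is "One-week pedometry producing at least 3 days of valid data with a minimum wear time of 10 h/day". Table 2 (Intervention section) lists the evaluation tools for this cohort as "PLAYself 1-week pedometry Self-report of regular sport/physical activity participation". The Data analysis section applies repeated measures ANOVA to "physical literacy scores, self-reported physical activity and rates of continued participation in physical activity" and explores moderation by dosage of "the relationship between time and the change in self-reported physical activity levels". The correlation and the multiple regression that follow refer to physical activity level without naming a measure.

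**Ages 13–18** (labelled 12–18 in Tables 1 and 3). Table 1 (Background section) lists four groups of primary hypotheses: health behaviours, life skills, academic outcomes and continued participation in sport. The academic one reads "Increase academic outcomes including school attendance, academic performance and high school graduation rates". The Data analysis section tests the "main effect of time on positive health behaviours and each of the six life skills". Academic outcomes then appear in Pearson correlations with other outcomes and in a logistic model for predictors of graduation. Continued participation appears in a multiple regression for predictors.

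**General statement.** The Background section says, without itemising, that repeated measures ANOVA will be used for the age-specific outcomes.

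**The concern.** The Study design section describes a single-arm, non-randomised, within-subject study. With no comparison group, the test of change from baseline is the main quantitative evidence for every hypothesis of an increase. An outcome left out of that test, or tested on a different measure, leaves its hypothesis without a matching analysis.

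At ages 6–12 the outcome affected is the only one measured by a device. Its named replacement is a report by children as young as 6, with adult help under age 8 (Data collection section), in a program that awards points for showing healthy behaviours (Incentivization section). Two candidate measures for one primary outcome also leave room to choose between them after data have been seen. The article plans preliminary analyses after 6, 12 and 24 months of recruitment.

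At ages 13–18, a correlation between a life skill and grade average, or a model of who graduates, cannot show that attendance or grades rose.

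**Working it through.** No figure in the plan bears on this point, so the check sets each Table 3 outcome beside the repeated measures analysis named for its cohort in the Data analysis section.

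| Cohort | Table 3 outcome | Named time test? |
|---|---|---|
| 6–12 | Physical literacy (PLAYself) | Yes |
| 6–12 | Activity minutes/day (pedometer) | No; a self-reported variable stands in its place |
| 6–12 | Continued engagement in sport | Yes |
| 13–18 | Six life skills | Yes, all six |
| 13–18 | Health behaviours (questionnaire) | Yes |
| 13–18 | Activity minutes/day (pedometer) | Not named; ambiguous |
| 13–18 | School attendance | No |
| 13–18 | Academic performance (grade average) | No |
| 13–18 | Academic attainment | No |
| 13–18 | Continued engagement in sport | No |
| 19–29 | Employment status, income, sport engagement | Yes, all three |

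**Count.**
- Ages 6–12: 2 of 3 matched.
- Ages 13–18: 6 + 1 = 7 of 12 matched, 4 unmatched and 1 ambiguous.
- Ages 19–29: 3 of 3 matched.
- Overall: 2 + 7 + 3 = 12 of 18 matched, 1 + 4 = 5 unmatched and 1 ambiguous.

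**Could self-reported activity at 6–12 be another name for a listed outcome?** The only self-report activity item for this cohort is regular participation. The same ANOVA sentence lists participation as a separate third variable, so the second variable is something else. It sits where Table 3 has pedometry. The Healthy Behaviour Questionnaire has a physical activity component, but it is listed only for the middle cohort. The wording recurs in the moderation sentence, so a single slip of the pen is unlikely.

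**Was the pedometer dropped elsewhere?** No. The Data collection section has it worn for a week at each assessment and scored as moderate-to-vigorous minutes. The data are planned and scored, but no time test at 6–12 names them.

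**Is the gap for sport participation at 13–18 deliberate?** Nothing in the text says so. The paragraphs for 6–12 and 19–29 both put continued participation in the repeated measures analysis, and Table 1 states the hypothesis for all three cohorts.

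**Pedometry at 13–18.** Table 2 places it under Health Behaviour, next to the questionnaire. Table 3 lists activity minutes and health behaviours as separate outcomes. Under Table 2 the phrase positive health behaviours could include it; under Table 3 it does not.

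**Graduation.** Table 1 hypothesises a rise in the graduation rate. Graduation happens once, so a participant has no baseline value from which to rise, and there is no control arm. A within-subject time test cannot address it.

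**The case against.** The strongest reply is that the Background section already promises repeated measures ANOVA for the age-specific outcomes, and that a journal article condenses a fuller plan. This has weight: a reader might infer that the investigators mean to leave these hypotheses untested, and the general statement does not support that. But the Data analysis section goes on to itemise which variables are tested in each cohort, and that list is narrower than the promise. This is not detail left to an analysis plan. The article states the analysis and states it inconsistently with its own tables.

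Four stronger readings are tempting and should not be made.

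- **That pedometry at 6–12 is collected and never analysed.** The correlation and the regression use a physical activity level with no label, and the regression is meant to cover all three primary outcomes. That level may well be pedometry. What can be said is that the measure is unspecified there and wrong for the tables in the time and moderation analyses.
- **That pedometry at 13–18 certainly has no time test.** Table 2's grouping allows the opposite reading. The defect is that two tables classify it differently and the analysis does not name it.
- **That the academic hypothesis gets no analysis at all.** It gets correlations and a graduation model that includes dosage. It lacks a named test of change.
- **That the sample of 100 was justified on pedometry.** The Sample size section cites "physical activity status, and physical activity levels" among the variables for this cohort, but does not say how they were measured.

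It is also fair to say that the direction and size of any self-report bias are not given, and that the incentives could change behaviour during a pedometer week too. The point does not depend on a direction of bias; the mismatch is enough.

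**Conclusion.** Wrong as written, on two counts. At ages 6–12, one of three primary outcomes is tested over time, and examined for moderation by dosage, on a variable with no listed instrument, while the defined device measure has no named time test. At ages 13–18, the hypotheses of increased attendance, academic performance and continued sport participation have no named test of change. Academic attainment is likewise not named. Pedometry at 13–18 is a third, lesser matter: an inconsistency between Tables 2 and 3 to be settled.

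This rests on reading the Data analysis lists as complete for each cohort and on treating the 12–18 label in Tables 1 and 3 as the 13–18 cohort. If a separate analysis plan itemises the missing tests, the practical harm is smaller, but the article still contradicts its own tables.

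**What to change.** **Ages 6–12 paragraph.** Replace self-reported physical activity with pedometer moderate-to-vigorous minutes per day in the time and moderation analyses. State that physical activity level in the correlation and regression is the same measure. If a self-report measure is also wanted, add its instrument to Table 3 and label it supportive.

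**Ages 13–18 paragraph.** Add change-over-time models for attendance and grade average. Add a repeated-measures model for binary data for continued participation, assuming it is recorded as yes or no. Name pedometer minutes per day explicitly as a time-tested outcome, and make Tables 2 and 3 agree on where it belongs.

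**Graduation.** Report it descriptively, or reword the hypothesis so that it does not claim an increase.

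**Cost.** A few sentences and a few more models, with no new data collection. There will probably be fewer valid pedometer records than self-reports, because a record needs at least 3 valid days of at least 10 hours' wear. The number of valid records at each assessment should be reported with the result.
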